### Data analysis plan

Baseline data will be analysed descriptively by allocated group. All data will be analysed on an intention-to-treat basis (*i.e*., participants will be assigned to the site where they were employed at randomisation even if they subsequently moved to another participating site). Analyses will be performed by an analyst who was not involved in data collection and is blinded to group identification, using either SAS (SAS Institute, Cary, NC, USA) or Stata (StataCorp LP, College Station, TX, USA), and supervised by a biostatistician ([name]).

For the primary analysis, differences between intervention and control groups in the primary outcome at Time 3 will be analysed using linear regression models adjusted for stratification by type of aged care (RACF/CACS) and clustering by site. Other outcomes, such as those for H_2_ and H_3_, which are measured at the cluster level, will be compared by cluster-level analysis, for example, using a negative binomial model stratified by type. All outcomes will similarly be compared at Time 2 to determine the short-term effect of the intervention. In secondary analyses, potential confounders, both at the cluster and individual level, will also be adjusted for, including baseline values of the outcome variables. Potential individual-level confounders include age, gender, previous aged care training/education, and length of time participants have worked in aged care.

An economic evaluation of the CLiAC program will be undertaken using the costs and outcomes (consequences) data discussed above. The first task will involve identifying, measuring and valuing the relevant costs and consequences of the intervention and usual practice (control group). The total costs include the cost of the CLiAC program facilitator, expert education consultant, and educational material. Quantities of resource use will be measured and unit costs (prices) will be assigned, including the cost of mentoring the CLiAC facilitator and implementing the program, using current pay rates (see HR data provided by collaborating organisation) and commercial rates (prices). The outcomes to be explored in the evaluation are: (a) the scores on the work environment measure (WES-R), effectiveness of leadership style (MLQ), person-centred care (P-CAT), and workforce dynamics (WDQ) assessed by staff; and (b) staff turnover and absenteeism. All outcomes (consequences) will be measured in natural units.

The second task will involve comparing changes in the total costs and total outcomes for these groups. This will comprise an incremental analysis of the costs and consequences of the CLiAC program; comparing the additional costs generated by the program over usual practice with the additional outcomes generated by the intervention in terms of: (a) scores on WES-R, MLQ, P-CAT and WDQ assessed by staff; and (b) staff turnover and absenteeism using the HR data. The results of the costs and outcomes will be presented separately (*i.e*., in a cost-consequence analysis) and in several cost-effectiveness ratios (such as a cost per unit change in staff turnover, cost per unit change in absenteeism).

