**Methods:**

Twenty-four residential and community aged care sites were recruited as managers at each site agreed in writing to participate in the study and ensure that leaders allocated to the control arm would not be offered the intervention program. Sites undergoing major managerial or structural changes were excluded. The 24 sites were randomly allocated to receive the CLiAC program (intervention) or usual care (control), stratified by type (residential vs. community, six each for each arm). Treatment allocation was masked to assessors and staff of all participating sites. The objective is to establish the effectiveness of the CLiAC program in improving work environment, workforce retention, as well as care safety and quality, when compared to usual care. The primary outcomes are measures of work environment, care quality and safety, and staff turnover rates. Secondary outcomes include manager leadership capacity, staff absenteeism, intention to leave, stress levels, and job satisfaction. Differences between intervention and control groups will be analysed by researchers blinded to treatment allocation using linear regression of individual results adjusted for stratification and clustering by site (primary analysis), and additionally for baseline values and potential confounders (secondary analysis). Outcomes measured at the site level will be compared by cluster-level analysis. The overall costs and benefits of the program will also be assessed.

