### Participants and sampling frame

Participants are both the care staff and the middle managers of the targeted residential and community aged care services. The sample size calculation was based on the primary outcome, participants’ perceived work environment: the subscales of the Work Environment Scale-R (WES-R) [26]. The study has 80% power to detect a difference of 0.49 standard deviations between groups as significant at the 5% level. This assumes that at least 20 clusters (sites) each with a minimum of 30 participants will complete the study, and that the intra-cluster correlation coefficient (ICC) is 0.26 (average estimate from a recent nursing home staff training intervention carried out in England and Wales) [27], giving a design effect of 8.54. The detectable difference is consistent with the WES-R [26] test developer’s recommendation that half a standard deviation represents a meaningful change on the instrument ([name], personal communication, Dec. 4, 2008). Consequently, the study will be able to detect a meaningful difference between the trial groups, and it is practical and feasible in terms of study design and data collection.

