### Aged care managers and care staff surveys

The self-administered outcome evaluation survey for managers and care staff combines both previously published and validated scales to measure the outcomes of interest. Table 2 provides details of the outcome measures included in the survey and how they relate to each of the hypotheses. In addition, the evaluation survey collates manager and staff demographic information including: age, gender, country of birth, year that employment commenced at the present service, current site and current job role, current title, programs involved in, employment status (full/part-time), professional background, experience in aged care/dementia care (years), highest level of education, aged care specific training, the type of dementia/aged care training or education completed, and the type of leadership/management training or education completed. The surveys were administered at baseline (Time 1), and repeated nine months from baseline (Time 2) and nine months after completion of Time 2 (Time 3). At Time 3, an additional two open-ended questions were added to the staff survey asking them to describe their experience of leadership and management at their site over the past six months and whether they have noticed any changes, plus a general comments question.

**Table 2 T2:** Outcome measures

**Instrument**	**Description of the instrument & domains**	**Hypotheses & measures**
Approaches to Dementia Questionnaire (ADQ) [29]	19 items that measure staff attitudes toward dementia care that reflects their understanding of the need to provide person-centred care for people with dementia. Likert scale ranging from 1 to 5 (strongly agree/disagree). Higher scores indicate a greater understanding of the need to provide person-centred care for people with dementia.	H_2_ – Care quality
Person-centred Care Assessment Tool (P-CAT) [30]	13 items that measure the extent to which staff rate their residential aged-care setting to be person-centred and providing best quality care for people with dementia. Responses are on a Likert scale ranging from 1 to 5 (‘disagree completely’ to ‘agree completely’). Higher scores indicate higher person-centred and quality care.	H_2_ – Care quality

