### Trial status

We are currently in the process of completing data collection. All manager and staff surveys have been collected. We are finalising collection of the final round of Human Resource and clinical indicator data. It is expected that data cleaning and analysis will begin in the next month and will be finalised by December 2013. Two of the 24 sites were disqualified after Time 2 based on Rule 1. So far, on average, 81% of manager surveys and 41% of staff surveys have been returned.

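### With about 22 sites, the negative binomial model named for the site-level primary outcomes would, under its usual tests, reject a true null about 6.5–10% of the time at a nominal 5%

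*Protocol article*

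**What the plan says.** The Data analysis plan section names two analyses.

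- **Work environment at Time 3:** it "will be analysed using linear regression models adjusted for stratification by type of aged care (RACF/CACS) and clustering by site".
- **Outcomes measured at site level, citing H2 (care quality and safety) and H3 (turnover):** these "will be compared by cluster-level analysis, for example, using a negative binomial model stratified by type".

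The same comparisons are to be repeated at Time 2. SAS or Stata will be used, with no procedure named. The section does not give a standard-error estimator, a z or t reference distribution, or degrees of freedom.

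The Abstract describes the allocation as "stratified by type (residential vs. community, six each for each arm"), which makes 24 sites. Trial status reports: "Two of the 24 sites were disqualified after Time 2 based on Rule 1". The note under Table 3 defines each indicator as a six-month event total divided by the mean number of clients, per site.

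**The concern.** A site-level outcome gives one observation per site, so each comparison rests on 22 or 24 numbers. Negative binomial regression estimates the between-site dispersion by maximum likelihood. With so few observations this takes no account of the parameters already fitted, so the dispersion comes out too small on average. The Wald and likelihood-ratio tests then use normal or chi-square critical values, as if the dispersion were known. Both errors make the interval too short and the p-value too small.

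At stake is the false-positive rate for outcomes that the article lists as primary. A claim that the programme reduced turnover or adverse events would carry more than the stated 5% risk of error.

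**Working it through.** **1. Number of units.** Two types × two arms × 6 = 24 sites. The disqualification rules in the site recruitment section apply to intervention sites only, so Time 3 has 24 − 2 = 22 sites, 10 against 12. With intercept, arm and type fitted, the residual degrees of freedom are 22 − 3 = 19 at Time 3 and 24 − 3 = 21 at Time 2.

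**2. The plan's own figures.** The target level is 5% (taken as two-sided): "The study has 80% power to detect a difference of 0.49 standard deviations between groups as significant at the 5% level". The inputs in the section on participants and sampling frame are 20 sites, 30 staff per site and an ICC of 0.26. The design effect reproduces: 1 + (30 − 1) × 0.26 = 8.54. The detectable difference does not: with 10 sites of 30 per arm, (1.960 + 0.842) × √(2 × 8.54/300) = 0.67 SD, not 0.49. That is a separate matter and does not enter below. The ICC and site size are used in step 5.

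**3. Size expected from theory.** Take a linear model on 22 equally precise site values.

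- Unbiased variance, z critical value: P(|t₁₉| > 1.960) = 6.5%.
- Maximum-likelihood variance (residual sum of squares divided by 22, not 19), z critical value: the effective threshold is 1.960 × √(19/22) = 1.821, and P(|t₁₉| > 1.821) = 8.4%. With 24 sites it is 1.960 × √(21/24) = 1.833, which gives 8.1%.

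This is only a guide for the negative binomial, where the dispersion plays the part of the residual variance.

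**4. Negative binomial, null simulation.** There were 22 sites, two types, two intervention sites lost and a log-client offset. Assumed: a mean of 60 clients per site (CV 0.4), with rates and dispersions as shown. Each row has 5,000 runs, with Monte Carlo error of about 0.3 to 0.4 points.

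| Events per client in 6 months | Dispersion | Wald z | Likelihood ratio | t on site log rates |
|---|---|---|---|---|
| 0.5 | 0.1 | 9.5% | 8.1% | 5.2% |
| 0.5 | 0.5 | 8.8% | 7.3% | 5.0% |
| 0.1 | 0.25 | 8.6% | 7.1% | 4.6% |
| 0.1 | 1.0 | 9.8% | 7.8% | 6.0% |
| 1.0 | 0.25 | 7.8% | 6.7% | 4.9% |

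Putting t critical values on the Wald statistic still gave 6.4% to 7.7%, so the critical value is only part of the problem. A robust variance with z was worse, at 8.8% to 12.3%. A separate simulation gave 7.8% to 9.8% (Wald), 6.5% to 8.6% (likelihood ratio) and 4.0% to 5.9% (t on log rates). With all 24 sites, as at Time 2, the figures were 7.1% to 8.8%, 6.3% to 7.0% and 4.3% to 5.2% (2,000 runs per setting).

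**5. Linear model for staff scales, 22 sites, mean 30 per site.** Site-size variation is assumed. The first five rows use ICC 0.26 or 0.05 and a size CV of 0 or 0.6.

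| Implementation | Size at nominal 5% |
|---|---|
| Cluster-robust, z | 7.6–10.8% |
| Cluster-robust, finite-sample factor, t on sites − 1 | 5.9–8.0% |
| Random site effect, ML, z | 8.2–9.6% |
| Random site effect, REML, z | 6.0–7.2% |
| Random site effect, REML, t(19) | 4.4–5.8% |
| Regression on site means, t(19) | 4.6–5.0% |

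A second run at ICC 0.26, with size CV 0.1, 0.4 and 0.6, gave 8.5%, 9.6% and 11.2% for cluster-robust z. With t(21) it gave 6.1%, 7.3% and 8.9%, and on site means 4.9%, 4.7% and 4.9%.

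**The case against.** The strongest reply is that the article commits to none of the liberal tests. It names no standard error or reference distribution, and such detail commonly sits in a statistical analysis plan, which is not shown. The negative binomial is introduced only as an example, so a t test on log rates would also meet the commitment to a cluster-level analysis. Adjustment for clustering by site likewise covers a REML mixed model with small-sample degrees of freedom. The rates, dispersions and site-size variation in the simulations are assumptions.

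Much of this stands. A reader might infer that the plan relies on large-sample standard errors throughout and so has a 6–11% error rate. The text does not support that, and for the staff scales the inflation is conditional on an implementation that the article leaves open. What does not fall away is that the only concrete model offered for the site-level outcomes missed 5% under both of its usual tests in every setting tried.

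A reader might also infer that the two staff scales assigned to H2 in Table 2 would be put through a count model, because the Data analysis plan cites H2 among outcomes measured at cluster level. One of them, the P-CAT, has "13 items that measure the extent to which staff rate their residential aged-care setting to be person-centred", which is an individual rating. The inference is not supported. The Abstract sends individual results to linear regression and only site-level outcomes to cluster-level analysis, and the quality indicators collated by each site are the natural referent. The wording is loose, no more.

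**Conclusion.** The concern holds for the site-level primary outcomes. The model named as the example, run with its usual Wald or likelihood-ratio test on 22 sites, would reject a true null about 6.5% to 10% of the time. With 24 sites the excess is only a little smaller. This rests on assumed event rates (0.1 to 1.0 per client), dispersion (0.1 to 1.0) and site sizes. The direction was the same throughout that range and agrees with the theoretical guide.

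For the staff scales the finding is conditional: about 6% to 11% if cluster-robust or z-based inference is used, depending on site-size variation and critical values, and close to 5% under other methods that the same wording allows. The point deserves correction before analysis, but it does not show that the plan has fixed an invalid test for work environment.

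**What to change.** **Site-level outcomes (quality indicators, turnover).** Make a small-sample method the main analysis. There are two options:

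- Linear regression of site log rates on arm and type, with t on sites minus parameters (19 df with 22 sites). State how zero counts are handled. They matter: at 60 clients, 0.1 events per client and dispersion 1.0, the expected count is 6 and the chance of a zero is 1/(1 + 6) = 14%, or about 3 of 22 sites.
- A permutation test over the allocations that met the restricted-randomisation criteria, stating how the two disqualified sites are treated.

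Keep the negative binomial model, with client numbers as offset, as a sensitivity analysis.

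**Staff scales.** Specify a mixed model with a random site effect, fitted by REML with Kenward-Roger degrees of freedom, or regression on site means with t critical values.

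**Cost.** Only the analysis wording changes. The regression and mixed-model options are available in the named software, and the article reports that analysis had not begun. Intervals become slightly wider. The critical value alone adds about 7% (2.093/1.960 = 1.07). Against a maximum-likelihood z interval in the linear case of step 3, the increase is about 15% (2.093/1.821 = 1.15).

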### Randomisation and blinding

After recruitment of the 24 sites to the study and collection of baseline (Time 1) data from all sites, the sites were allocated to either the intervention or control arm by a biostatistician ([name]) who was not involved in recruitment, data collection, or contact with the sites. Sites were stratified by type of aged care (RACF vs. CACS). Within each stratum, restricted randomisation was used to balance the groups by: size of the service (number of clients), span of control (care staff to middle management ratio), and geographical location (rural vs. urban) [28]. Location is balanced exactly, while for size and span of control the means of the two groups are allowed to differ by no more than 10% in relative terms (*i.e*., ratio of means between 0.9 and 1.1). Allocation was thus fully concealed. The sites were notified by email and completed a written agreement to abide by the random allocation. Also, in an attempt to reduce bias associated with staff becoming aware of managers attending the CLiAC program, participating managers signed forms agreeing not to discuss with their work teams and staff any group specific activities or training that have occurred, and agreed to maintain blinding until the end of data collection. The members of the research team responsible for data entry and analysis will remain blind until completion of the main analysis.

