### Recruitment: middle managers and care staff

Recruitment of aged care middle managers and care staff to the study was based on the eligibility criteria shown in Table 1. All staff employed at each site at each data collection time were eligible to participate. An invitation letter and a set of questionnaires were sent to all eligible staff of the participating sites from the research team. Return of their questionnaire was considered as consent (implied consent).

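### The primary model leaves the pre-randomisation baseline outcome to secondary analyses; adding the Time 1 site mean would cost almost nothing and could raise precision

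*Protocol article*

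**What the plan says.** Under Data analysis plan, the protocol article says that the main comparison of the arms, made on the Time 3 results, "will be analysed using linear regression models adjusted for stratification by type of aged care (RACF/CACS) and clustering by site". The next step is separate: "In secondary analyses, potential confounders, both at the cluster and individual level, will also be adjusted for, including baseline values of the outcome variables". The Methods paragraph of the abstract makes the same split between primary and secondary analysis.

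Three other statements bear on the choice:

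- **Timing of baseline.** Randomisation and blinding says that allocation came "After recruitment of the 24 sites to the study and collection of baseline (Time 1) data from all sites". Every site therefore has a baseline measured before allocation.
- **Who is surveyed.** Recruitment: middle managers and care staff says: "All staff employed at each site at each data collection time were eligible to participate". The respondents are an open sample at each wave. Time 3 comes about 18 months after Time 1.
- **Response.** Trial status reports that "on average, 81% of manager surveys and 41% of staff surveys have been returned".

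The article does not say whether baseline values means a respondent's own earlier score or the mean of the site.

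**The concern.** In a trial with few sites and a high ICC, the treatment contrast is limited by how much sites differ from each other. Extra respondents per site help little, and no further sites can be added at this stage. A measure of the same outcome at the same site before allocation is then an obvious covariate, because it can explain part of the between-site variation that dominates the standard error. Leaving it out of the primary model may mean a wider confidence interval than the data require, and the trial has little precision to spare.

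The level of the covariate matters too. A site mean exists for every Time 3 respondent. A respondent's own Time 1 score exists only for those who were employed then and returned a survey then. A model that needed it would be restricted to people who stayed, and staff turnover is itself a primary outcome (H3).

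**Working it through.** **Inputs from the article (Participants and sampling frame; Trial status; Recruitment of targeted aged care sites).** m = 30 participants per site, ICC = 0.26, 80% power, 5% level (taken as two-sided), target 0.49 SD. Of the 24 sites, two were disqualified under the first disqualification rule. That rule concerns intervention sites, so I take 10 intervention and 12 control sites.

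**Input not in the article.** The cluster autocorrelation (CAC) is the correlation of a site's true level between Time 1 and Time 3. I assume 0.3 to 0.9.

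**1. The plan's own figures.** Design effect = 1 + 29 × 0.26 = 8.54, as stated. The detectable difference with 10 sites per arm is (1.960 + 0.842) × √(2 × 8.54 / 300) = 0.668 SD by the normal approximation. The stated 0.49 SD does not reproduce from 20 sites in total. That is a separate point about the sample size. It is used here only to show that precision is short.

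**2. Share of variance between sites.** Variance of a site mean = 8.54/30 = 0.2847 (in SD² units), of which 0.26 is between sites: 0.26/0.2847 = 7.8/8.54 = 0.913, or 91%.

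**3. Unadjusted contrast, 10 against 12 sites.** SE = √[0.2847 × (1/10 + 1/12)] = √0.0522 = 0.2284. With arm and type in the model there are 22 − 3 = 19 df, so the detectable difference is 0.2284 × (2.093 + 0.861) = 0.67 SD. Power at 0.49 SD (noncentral t) is 53%.

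**4. Adjusted for the Time 1 site mean.** With separate respondents at each wave, the correlation of a site's two means is r = m × ICC × CAC / design effect = 7.8 × CAC / 8.54. The variance is multiplied by 1 − r². With 18 df, the detectable difference is SE × (2.101 + 0.862).

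| CAC | r | variance cut (r²) | SE | detectable difference | power at 0.49 SD |
|---|---|---|---|---|---|
| 0.3 | 0.274 | 7.5% | 0.220 | 0.65 SD | 56% |
| 0.5 | 0.457 | 21% | 0.203 | 0.60 SD | 63% |
| 0.6 | 0.548 | 30% | 0.191 | 0.57 SD | 68% |
| 0.7 | 0.639 | 41% | 0.176 | 0.52 SD | 75% |
| 0.8 | 0.731 | 53% | 0.156 | 0.46 SD | 84% |
| 0.9 | 0.822 | 68% | 0.130 | 0.39 SD | 94% |

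**5. Where 0.49 SD is reached.** The SE must be 0.49/2.963 = 0.165, so 1 − r² = (0.165/0.2284)² ≈ 0.52, r ≈ 0.69 and CAC ≈ 0.69 × 8.54/7.8 ≈ 0.75.

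**6. Worst case.** If the baseline predicted nothing (r = 0), the detectable difference would be 0.2284 × 2.963 = 0.677 SD, against 0.675 SD unadjusted.

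**7. Own score or site mean.** If response at the two waves were independent at the average staff return of 41%, about 41% of Time 3 staff respondents would also have a Time 1 survey, before allowing for turnover. The article gives no overlap figure, so this is only a guide.

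**The case against.** The strongest reply is that nothing is wrong with the plan. A Time 3 comparison adjusted for the stratification factor and clustering is unbiased under randomisation. Allocation already balances location exactly and keeps size and span of control within 10%, so chance imbalance is partly dealt with by design. The baseline-adjusted analysis is prespecified and will be run. The dispute is only over which model is called primary. All of this stands, and it is why the point is one of efficiency.

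The reply also disposes of three stronger readings that a reader might infer:

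- **That the secondary analysis relies on scores many Time 3 respondents lack.** The text allows covariates at cluster level as well as individual level. The individual-level confounders it then names are age, gender, training and time in aged care, and not the baseline outcome. A site mean fits the wording, and a separate analysis plan may settle it. Selection of stayers is a risk of one possible reading and is not a stated feature of the plan.
- **That adjustment would bring the trial to its half-SD target.** At CAC 0.6 or 0.7 it does not, and at 0.3 the gain is small. With open sampling and about 18 months between the waves, a high CAC cannot be taken for granted.
- **That this is the largest precision gain available.** Without a baseline to follow-up correlation this cannot be shown.

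The shortfall against 0.49 SD comes from the sample-size calculation and should not be used to raise the severity of this point.

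What the reply does not answer is that the covariate exists for every site, costs one degree of freedom and loses almost nothing even when it is useless.

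**Conclusion.** The concern holds as a free improvement and not as a must-fix error. The primary analysis is valid but probably less precise than the data allow. The gain from the Time 1 site mean runs from slight (variance cut 7.5%, detectable difference 0.65 SD) to large (68%, 0.39 SD) over CAC 0.3 to 0.9, against 0.67 SD unadjusted.

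These figures rest on 10 against 12 sites, 30 respondents per site at both waves, ICC 0.26, separate respondents at each wave and a two-sided 5% t test. The CAC is assumed throughout. The article does not fix the level of the baseline covariate. Open eligibility and the 41% staff return favour the site mean.

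**What to change.** Before unblinding, define the primary model as the Time 3 outcome regressed on arm, type (RACF/CACS) and the Time 1 site mean of the same outcome, with clustering by site. Report the model without baseline as a sensitivity analysis.

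State that the baseline covariate in the main models is the site mean. Any analysis using respondents' own Time 1 scores should be labelled exploratory, as it describes only those who stayed and answered twice.

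For turnover and the clinical indicators, add the site's rate from before randomisation only if such data exist. The article says that these data cover the study period and does not show that they start before allocation.

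The cost is a sentence or two in the analysis plan and one degree of freedom (t critical value from 2.09 to 2.10). Trial status says that analysis had not begun, and the analysts are to stay blinded until the main analysis is complete, so the change can still be prespecified.
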